### STOP intervention

The STOP treatment includes content designed to simultaneously and explicitly target both chronic pain and obesity. Treatment components are drawn from evidence-based interventions for chronic pain and obesity separately [11-13] and then integrated to influence both outcomes. Treatment begins with education about the relationship between chronic pain and overweight/obesity and an introduction to self-monitoring. Participants are given a daily calorie goal, taught how to log daily caloric intake, and encouraged to do so daily. The second session reviews the participant’s experience with logging calories. At this session, basic nutrition information, including portion sizes and how to read a nutrition label, is also reviewed. The importance of regular activity is discussed during session three, and while physical activity is encouraged activities are reframed to encourage engagement with any pleasant activity. Session four presents time-based activity pacing. During session five, interventionists work with patients to identify triggers for eating, low activity, and pain and develop a strategy to manage these triggers. Sessions six and seven focus on identifying, evaluating, and challenging automatic thoughts about pain and weight. Sessions eight and nine focus on identifying and challenging intermediate and core beliefs related to pain and weight. Session 10 discusses the importance of relaxation and teaches diaphragmatic breathing and progressive muscle relaxation. Finally, learned material is reviewed during session 11 and a plan for relapse prevention, flare up planning, and ongoing weight loss is discussed.

### Quantitative data collection

Data will be collected at various time points beginning at baseline and continuing through 12-month follow-up on continuous and dichotomous variables using the measures listed in Table 2. Anthropomorphic measures of weight, height and waist circumference will be collected at each weekly assessment session, as will measures of pain intensity and interference. Participants will be paid $30 to offset travel costs at the 12-month follow-up to encourage retention.

**Table 2 T2:** STOP table of measures

**Measures**	**Baseline**	**Week 1 & 11**	**Wks 2-10**	**3, 6, 12-month follow-up**
Health Behavior/Medical/Pain History Questionnaire	X			X
**Pain and eating behavior**				
West Haven Yale Multidimensional Pain Inventory (WHYMPI) [30]	X			X
Survey of Pain Attitudes (SOPA) [31]	X			X
Arthritis Self-Efficacy Scale (ASES) [32]	X			X
Pain Catastrophizing Scale (PCS) [33]	X			X
Dutch Eating Behavior Questionnaire (DEBQ) [34]	X			X
**Stage of change short forms**				
Exercise [35]	X			X
Weight [36]	X			X
Pain [37]	X			X
**Psychological measures**				
Quality of Life (SF-36) [38]	X			X
Primary Care Evaluation of Mental Disorders (PRIME-MD) [39]	X			X
Positive and Negative Affect Scale (PANAS) [40]	X	X	X	X
**Treatment credibility and preference**				
Therapy Evaluation Form [41]		X		
Treatment Preference Questionnaire		X		

### Sample size and power estimation

Input data to estimate sample size needed for adequate power came from pilot data from individuals with co-morbid chronic pain and obesity enrolled in standard care, healthy lifestyle, or intensive weight loss interventions [42] and published results from a study of weight loss intervention for older obese adults with knee osteoarthritis [43]. These data informed the following assumptions: (a) SCW is associated with an 11 pound weight loss, SCP is associated with a 1 pound weight loss, and STOP is associated with a 17 pound weight loss; (b) the within-person correlation of weight over measurements is 0.96 and the between-person standard deviation is 10 pounds; (c) SCP is associated with a 2-unit reduction in pain level (on a 10-point scale), SCW is associated with no reduction in pain level, and STOP is associated with a 4-unit reduction in pain level; (d) the within-person correlation of pain over measurements is 0.89 and the between-person standard deviation is 1.6 units; and (e) the correlation between pain level and pounds lost is 0.34. Additional assumptions included 85% retention rate over 12 months, maintenance in outcomes from 3- to 12-month follow-up, and .05 Type I error rate. Power and sample size estimates were calculated with the GLIMMPSE 2.0 online tool through Sample Size Shop’s tools for multilevel and longitudinal data [44]. A sample size of 120 participants will provide power in excess of 80% to detect between-group differences and within-person change over time while allowing for study attrition.

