### Primary aim

The primary aims of the proposed research are to determine whether overweight and obese individuals with chronic pain who are randomized to receive an integrated treatment Simultaneously Targeting Obesity and Pain (STOP) will show more weight loss and greater reduction in pain intensity over a 6-month period and greater maintenance at 12 months than those who receive standard care behavioral weight loss (SCW) or standard care behavioral pain management (SCP). We hypothesize that individuals randomized to receive the STOP treatment will demonstrate improved weight loss, pain reduction, and maintenance compared to standard care treatment approaches.

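### Greater maintenance at 12 months is a primary claim with no defined meaning; if it means less loss of benefit, the sizing inputs give it no effect and the stated power does not cover it

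*Protocol article*

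**What the plan says.** The Primary aim section separates two periods: more weight loss and pain reduction over 6 months, and better maintenance at 12 months. The hypothesis that follows lists maintenance as a third item: "STOP treatment will demonstrate improved weight loss, pain reduction, and maintenance compared to standard care treatment approaches". The Abstract repeats both statements.

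The section Sample size and power estimation gives one expected effect per arm and outcome. For weight: "SCW is associated with an 11 pound weight loss, SCP is associated with a 1 pound weight loss, and STOP is associated with a 17" (the last figure is also in pounds). For pain, the assumed reductions are 2 units (SCP), 0 units (SCW) and 4 units (STOP). It adds 85% retention and "maintenance in outcomes from 3- to 12-month follow-up, and .05 Type I error rate". It concludes: "A sample size of 120 participants will provide power in excess of 80% to detect between-group differences and within-person change over time".

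The section Quantitative data analysis makes linear and quadratic group-by-time interactions the primary tests, over baseline, 3, 6 and 12 months. It says they will also show how far any between-group differences persist. No section defines maintenance as a quantity to be estimated.

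**The concern.** Maintenance can mean two things here, and the plan supports only one of them.

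- **Less loss of benefit:** STOP participants regain less weight, or lose less of their pain improvement, after treatment ends. The separate listing in the hypothesis favours this reading, because otherwise the third item largely repeats the first two at a later visit.
- **Persisting difference:** the between-arm difference in change from baseline is still there at 12 months. The analysis section's wording about differences persisting allows this reading.

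On the first reading, the sizing assumption removes the effect that the hypothesis asserts. The primary model adds to the difficulty. It is said to inform on maintenance, but its terms mix the early treatment effect with later change. At stake is what the trial may conclude about durability: a large early effect could be reported as better maintenance, or a stable benefit could be described as fading.

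**Working it through.** **Inputs (Sample size and power estimation, Study design).** Weight: SD 10 lb, within-person correlation 0.96. Pain: SD 1.6, correlation 0.89. N = 120 in three arms with 85% retention. Assumed here, because not stated: equal allocation (40 per arm, 0.85 × 40 = 34 retained), two-sided alpha 0.05, and the same correlation between all pairs of visits.

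**Step 1: the plan's own figure, for change from baseline.** SD of change = SD × √(2(1 − ρ)); SE of a difference = SD of change × √(2/n).

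- Weight: 10 × √0.08 = 2.83 lb; SE = 2.83 × √(2/34) = 0.686 lb. Effect 17 − 11 = 6 lb; power above 99.9%.
- Pain: 1.6 × √0.22 = 0.75 units; SE = 0.75 × √(2/34) = 0.182 units. Effect 4 − 2 = 2 units; power above 99.9%.

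The bound of 80% is reproduced when the stated correlations are used. With the raw SD of 10 lb and no use of the correlation, weight would have 69.6%. The exact settings of the plan's calculation are not shown, so only the bound can be checked.

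**Step 2: what the inputs imply for maintenance.** With outcomes held from 3 to 12 months, STOP's assumed advantage at 0, 3, 6 and 12 months is (0, 6, 6, 6) lb over SCW and (0, 2, 2, 2) units over SCP.

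| Contrast | Weight | Pain |
|---|---|---|
| 12 months minus baseline | 6 lb | 2 units |
| 12 months minus 3 months | 6 − 6 = 0 lb | 2 − 2 = 0 units |
| 12 months minus 6 months | 6 − 6 = 0 lb | 2 − 2 = 0 units |

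The first row has power of about 100%. The other two rows have no assumed effect, so no sample size can be said to power them.

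**Step 3: what 120 participants could detect.** Detectable difference at 80% power = (1.96 + 0.84) × SE. At 34 per arm this is 2.80 × 0.686 ≈ 1.9 lb and 2.80 × 0.182 ≈ 0.51 units. Smaller differences have less power: 1 lb gives 31% and 0.25 units gives 28%. The figures depend on the correlation. If it were 0.5 to 0.9 from 3 to 12 months (an assumed range), the detectable weight difference would be 6.8 to 3.0 lb.

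**Step 4: the planned primary terms on the plan's own profile.** A generalised least-squares fit of linear and quadratic group-by-time terms, with no group difference at baseline and 34 per arm, gives STOP's fitted advantage at t months:

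- Weight: 1.724t − 0.1064t², which is 4.2, 6.5 and 5.4 lb at 3, 6 and 12 months. |z| = 8.9 (linear) and 7.0 (quadratic).
- Pain: 0.578t − 0.0357t², which is 1.4, 2.2 and 1.8 units. |z| = 11.4 and 9.0.

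The true profile is flat after 3 months, so these terms are significant only because of the drop from baseline to 3 months. A quadratic cannot follow a drop and then a plateau. From 6 to 12 months it shows an apparent loss of 6.51 − 5.36 = 1.15 lb (SE 0.605, |z| = 1.9) and 2.18 − 1.80 = 0.39 units before rounding of the fitted values (SE 0.160, |z| = 2.4). From 3 to 12 months the same curve rises by the same amounts. Neither movement is in the assumed data.

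**The case against.** The strongest reply is that the plan never claims power for a difference in later change. Its power sentence speaks of "power in excess of 80% to detect between-group differences and within-person change over time", and maintenance enters that section only as an input. The aim names a time point, and the analysis section speaks of differences persisting. Read that way, maintenance is the 12-month difference, and power is about 100% on the plan's inputs. This reading is available and stands as one of two. It does not explain why the hypothesis lists maintenance separately, so the wording still needs to be settled.

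A reader might also infer more than the document supports:

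- **That power is 5% against a stated 80%.** These are different quantities. A test with zero assumed effect rejects at its alpha, but the 80% was not stated for that test.
- **That the plan predicts a non-significant maintenance test.** No contrast between 3 or 6 months and 12 months is specified. The specified interaction terms are expected to be strongly significant.
- **That 120 is too few.** Step 3 does not show this. What is missing is a stated effect.
- **That the plan says every arm fully maintains its result.** This is inferred. The assumption is unqualified and gives no regain figure, so flat means are the plain reading, but the article does not spell it out by arm.

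**Conclusion.** The concern holds in conditional form. If greater maintenance means less loss of benefit after treatment, the sizing inputs give it an effect of 0 lb and 0 units, and the power above 80% does not extend to it. If it means a difference in change from baseline still present at 12 months, the 6 lb and 2 unit inputs cover it. The document does not say which is meant.

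Under either reading, the linear and quadratic interaction terms are a poor basis for statements about maintenance. On the plan's own flat profile they suggest fading of about 1.1 lb and 0.39 units between 6 and 12 months. These sizes rest on equal allocation, 34 per arm, equal correlation between visits, and flat means in every arm from 3 to 12 months. The apparent fading itself does not depend on sample size; at 40 per arm its |z| rises to 2.1 for weight and 2.6 for pain.

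**What to change.** 1. In the Primary aim and the Abstract, replace the maintenance claim with the between-arm difference in change from baseline at 12 months: STOP versus SCW for weight and STOP versus SCP for pain.
2. In Sample size and power estimation, state that the sample size was not set for a between-arm difference in 6-to-12-month change.
3. In Quantitative data analysis, report that difference as an estimate with its confidence interval, from visit-specific means (time as a categorical factor), and not from the linear and quadratic group-by-time terms.

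Nothing changes in sample size, visits or treatment. The cost is a few sentences, recorded as an amendment because a primary aim of a registered trial is reworded, and one primary claim that becomes more modest.

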### Quantitative data analysis

Longitudinal outcomes will be analyzed on an intent to treat basis, including every subject who is randomized regardless of protocol adherence, study completion, or missing data. Generally, our approach will be to use mixed-effects regression models (MRMs) implemented via SAS PROC MIXED. These models do not place restrictions on the number of observations per individual; therefore, no participants will be excluded from the analysis due to missing data. In addition to using all available data, mixed models are appropriate for this study because they model individual change across repeated measures, fixed effects of baseline characteristics and treatment group, and interactions between fixed effects and continuous time [45].

For each outcome (pain intensity, weight), standard care serves as the control. For pain outcomes, STOP versus SCP and SCW versus SCP contrasts will be estimated; for weight outcomes, STOP versus SCW and SCP versus SCW contrasts will be estimated. Following the recommendations of Fitzmaurice and colleagues [46], we will model our primary outcomes at all timepoints (baseline, 3-month follow-up, 6-month follow-up, and 12-month follow-up), include both linear and quadratic effects of time and group by time interactions, control for baseline weight and baseline pain intensity, and assume the group means and variances are equal at baseline because subjects are randomized to group. Our primary tests will be for the group by time interaction terms which will indicate the extent to which treatment groups experience change in weight and pain intensity following baseline and the degree to which any observed differences are maintained over time.

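### A linear-plus-quadratic time curve cannot follow the drop-then-plateau course assumed for power, so arm differences are biased and a fully maintained benefit appears to fade

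*Protocol article*

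**What the plan says.** The Quantitative data analysis section fixes the mean model for both primary outcomes. Time is continuous: the models are said to handle "interactions between fixed effects and continuous time". Baseline is itself an outcome: "we will model our primary outcomes at all timepoints (baseline, 3-month follow-up, 6-month follow-up, and 12-month follow-up". The models "include both linear and quadratic effects of time and group by time interactions" and "assume the group means and variances are equal at baseline because subjects are randomized to group". The group-by-time terms are the primary tests. They are to show how much the arms change and "the degree to which any observed differences are maintained over time".

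The Sample size and power estimation section assumes "maintenance in outcomes from 3- to 12-month follow-up". Its effects are losses of 17 lb (STOP), 11 lb (SCW) and 1 lb (SCP), and pain reductions of 4 (STOP), 2 (SCP) and 0 (SCW) units. For weight, "the within-person correlation of weight over measurements is 0.96 and the between-person standard deviation is 10 pounds"; for pain, the correlation is 0.89 and the SD 1.6 units.

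The Primary aim section asks for greater change over 6 months and greater maintenance at 12 months. The article names no categorical, piecewise or lack-of-fit alternative for time.

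**The concern.** With the arms equal at month 0, each between-arm difference is forced into the form a·t + b·t². That is two parameters for three post-baseline differences. The course on which the trial is powered, zero at baseline and then a constant D, does not lie on such a curve. The error is in the mean curve, so naming the 6- or 12-month difference as the target does not cure it: the value read off the curve is still wrong.

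A parabola that rises steeply and then has to level off must turn down again. If STOP keeps its advantage completely, the fitted curve peaks and declines, and a reader who takes maintenance from the interaction terms, as the plan directs, would report a fading benefit. Under some covariance models the misfit also inflates the residual variance and so costs precision.

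**Working it through.** **Plan's own figure.** The article claims power above 80% with 120 participants. I assume 1:1:1 allocation (40 per arm, 34 after 15% loss) and a two-sided 0.05 level.

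- SD of weight change: 10·√(2·(1 − 0.96)) = 2.83 lb. SD of pain change: 1.6·√(2·(1 − 0.89)) = 0.75 units.
- With these SDs all four planned contrasts have more than 99% power, so the claim is met.
- With the raw SD of 10 lb, STOP versus SCW on weight would have 76.5% (40 per arm) or 69.6% (34 per arm).

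**Fitted curve, weight, STOP versus SCW.** The true advantage is d = (0, 6, 6, 6) lb at t = 0, 3, 6, 12. With equal arms, a common baseline and compound symmetry, the generalised least-squares fit of the difference is (a, b) = M⁻¹v.

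- Up to scale, the inverse covariance is I − cJ (J the all-ones matrix), with c = 0.96/(1 + 3·0.96) = 0.2474.
- Σt = 21, Σt² = 189, Σt³ = 1971, Σt⁴ = 22113.
- M₁₁ = 189 − c·21² = 79.887; M₁₂ = 1971 − c·21·189 = 988.98; M₂₂ = 22113 − c·189² = 13274.8.
- v = 6·(1 − 3c)·(21, 189) = (32.47, 292.27).
- Solution: a = 1.724, b = −0.1064.

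| Month | True (lb) | Fitted (lb) | Error |
|---|---|---|---|
| 3 | 6.0 | 4.21 | −30% |
| 6 | 6.0 | 6.51 | +9% |
| 12 | 6.0 | 5.36 | −11% |

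The curve peaks at −a/(2b) = 8.1 months, at 6.98 lb, and is 23% lower by month 12. From month 6 to 12 the false loss is 6.51 − 5.36 = 1.15 lb, or 18%.

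**Other planned contrasts.** Pain, STOP versus SCP (true 2.0): 1.41, 2.18, 1.80, a false loss of 0.39. Pain, SCW versus SCP: the same sizes with the sign reversed. Weight, SCP versus SCW (true 10 lb): 7.02, 10.85, 8.94, a false loss of 1.92 lb.

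**Sensitivity of the bias.** Across compound symmetry, a time-decaying covariance and independence, with common or separate intercepts, month 3 is 70–78% of the truth, month 6 is 109–118%, month 12 is 89–100%, and the 6-to-12-month fade is 14–18%. Its direction never changed.

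**How often the fade would be significant.** The change from month 6 to 12 is the contrast L = (6, 108).

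- L′M⁻¹L = 1.553, so with 34 per arm SE = √(2/34 · 100·0.04 · 1.553) = 0.605 lb.
- z = 1.149/0.605 = 1.90, so with covariance known the two-sided 0.05 test rejects in 48% of trials (54% with 40 per arm). For pain the figures are 67% and 74%.
- Simulation (400–600 trials, 34 per arm, estimated covariance, own-baseline covariate left out):

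| Contrast | Quadratic, random intercept | Quadratic, unstructured | Visit as factor |
|---|---|---|---|
| Weight, STOP–SCW | 18% | 50% | about 6% |
| Pain, STOP–SCP | 49% | 67% | 4–5% |

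The random-intercept rate is lower for weight because the misfit is absorbed into the residual variance: the model SE at month 6 is 0.92 lb, against 0.68 lb with visit as a factor.

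If the SD of weight change is 10 lb (correlation 0.5), the fit is nearly the same (4.38, 6.77, 5.57), but the false fade is significant in only about 7–10% of trials.

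**The case against.** The strongest reply is that the planned primary test is not damaged. The joint 2-df group-by-time test is valid when the arms do not differ and has power near 100% under the plan's inputs. That stands. But the plan also reads the degree of maintenance from the same terms, and this reading is what the misfit distorts.

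The article names no significance test of month 6 against month 12, so the false-fading percentages belong to a test defined here as one natural way to judge maintenance. They also depend on the covariance. Adding an assumed random slope with SD 0.1, 0.3 or 0.5 lb per month lowers the known-covariance rate for weight from 48% to 46%, 34% and 23%. They should be read as illustrations; the bias does not depend on them.

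At the time points of the primary aim the errors are modest: +0.5 and −0.6 lb on 6 lb, and ±0.2 on the pain scale. The −30% is at month 3.

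The bias depends on the true course. If 80% of the effect is reached at month 3 (true 4.8, 6, 6), the fit is 3.97, 6.24, 5.70. At 65% (true 3.9, 6, 6) it is 3.78, 6.03, 5.96, almost unbiased. The immediate plateau is, however, the course on which the trial is powered, and the primary model should be able to reproduce it.

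If baseline were only a covariate and each arm had its own level, a quadratic would fit three visits exactly. The article rules this out by listing baseline among the modelled outcomes, although its added adjustment for baseline values leaves the final model somewhat unsettled. Detail may be left to an analysis plan that is not shown, but the form of the time curve is stated here, so a plan that follows the article inherits the bias.

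**Conclusion.** The concern holds. Under the protocol's own assumptions, the stated model understates the advantage at month 3 by about 30%, overstates it at month 6 by about 9%, understates it at month 12 by about 10–11%, and turns complete maintenance into an apparent loss of about 18% between months 6 and 12. The exact figures assume compound symmetry at the stated SDs and correlations, equal allocation and no own-baseline covariate. The direction of the false fade was the same under every covariance and intercept structure tried. How often it would reach significance ranges widely with the covariance and the variability of change. The overall test of any arm difference is unaffected. Because maintenance at 12 months is part of the primary aim, this should be corrected before analysis.

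**What to change.** In the Quantitative data analysis section, replace the linear and quadratic time terms by visit as a four-level factor (baseline, 3, 6 and 12 months). Keep the equal-baseline constraint and use an unstructured covariance. Estimate the arm differences at 6 and 12 months, and the change in difference between them, from the visit terms. The fitted differences are then unbiased whatever the time course, and the 6-to-12-month change is zero when the advantage is maintained. The polynomial can stay as a descriptive secondary model.

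The change needs no new data and adds one parameter per contrast. With the weight inputs and 34 per arm, the visit-factor SE is √(2/34 · 100·(1 − 0.96²)) = 0.679 lb. The quadratic SE, using √(2/34 · 4 · L′M⁻¹L), is 0.664 lb at month 6 and 0.655 lb at month 12, so the increases are about 2% and 4%. For the 6-to-12-month change the SE is √(2/34 · 2 · 4) = 0.686 lb against 0.605 lb, about 13% larger. That is the price of an unbiased answer on maintenance.

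### The primary model uses each outcome's baseline twice, as a repeated outcome and as a covariate, which biases the standard errors of the group-by-time tests downward

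*Protocol article*

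**What the plan says.** The Quantitative data analysis section of the protocol article describes one model for each primary outcome (weight, pain intensity):

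- Model class: the plan is to "use mixed-effects regression models (MRMs) implemented via SAS PROC MIXED". No covariance structure is named.
- Outcome vector: "we will model our primary outcomes at all timepoints (baseline, 3-month follow-up, 6-month follow-up, and 12-month follow-up".
- Time: the model will "include both linear and quadratic effects of time and group by time interactions".
- Baseline: the model will "control for baseline weight and baseline pain intensity, and assume the group means and variances are equal at baseline".
- Primary test: "Our primary tests will be for the group by time interaction terms".

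The Sample size and power estimation section gives the variance inputs. For weight, "the within-person correlation of weight over measurements is 0.96 and the between-person standard deviation is 10 pounds"; for pain, the correlation is 0.89 and the SD 1.6 units. It also assumes "85% retention rate over 12 months, maintenance in outcomes from 3- to 12-month follow-up, and .05 Type I error rate".

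**The concern.** There are two standard ways to use a baseline measurement. One keeps it as the first repeated outcome and constrains the arm means to be equal there (constrained longitudinal analysis). The other removes it from the outcomes and enters it as a covariate (analysis of covariance). Each is valid alone. The section lists both for the same model, so at the baseline row the outcome and one of its predictors are the same number.

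A random-effects model then estimates a coefficient near 1 for that predictor. The baseline residual nearly vanishes, and the model fits one variance structure to all four visits although the baseline row no longer varies. The group-by-time standard errors can come out too small. At stake is the false-positive rate of the primary tests on both primary outcomes. Power is not at issue.

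**Working it through.** **The plan's own figure.** Assume 1:1:1 allocation (40 per arm, 34 after 15% loss) and two-sided 0.05.
- Weight: change SD = 10 × √(2 × 0.04) = 2.83 lb; SE of an arm difference = 2.83 × √(2/34) = 0.69 lb; planned STOP–SCW difference 17 − 11 = 6 lb, about 8.7 SE.
- Pain: change SD = 1.6 × √(2 × 0.11) = 0.75; SE = 0.18; planned STOP–SCP difference 4 − 2 = 2 units, about 11 SE.

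Power is close to 1 for both, so the stated bound of more than 80% holds.

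**Why the standard error shrinks (weight, random intercept).**
1. Within-person variance is 100 × (1 − 0.96) = 4; between-person variance is 96.
2. Take the baseline coefficient as 1, its approximate fitted value. The residuals are 0, e1−e0, e2−e0, e3−e0. Their true variance is 0 at baseline and 8 at each follow-up, with covariance 4 between follow-ups.
3. The model imposes one variance and one covariance. The variances sum to 24 and all matrix elements to 3 × 8 + 6 × 4 = 48. Fitted within-person variance = (24 − 48/4)/3 = 4. Fitted intercept variance = 48/16 − 4/4 = 2.
4. The model therefore works with variance 6 and covariance 2 at every visit, where the follow-ups really have 8 and 4. Generalised least squares with these two matrices (common intercept, linear and quadratic time by arm) gives a model SE about 0.75 of the true SE at 6 months and 0.83 at 12 months.
5. Implied two-sided error: 2Φ(−1.96 × 0.75) ≈ 14% at 6 months; 2Φ(−1.96 × 0.83) ≈ 10% at 12 months. The ratios are scale-free, so pain gives the same.

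**Simulation, no arm difference and no mean change.** N = 120, compound-symmetric data with the plan's SDs and correlations, REML, model as written. Ranges cover weight and pain, with and without 15% dropout (4000 runs for random intercept, 700 with a slope).

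| Test (nominal 5%) | Random intercept | Random intercept and slope |
|---|---|---|
| Group by time, all arms, 4 df | 16.7–18.7% | 12.9–16.9% |
| Group by time, STOP v control, 2 df | 12.8–14.9% | 10.4–14.7% |
| Linear term | 11.6–13.2% | 14.7–18.6% |
| Quadratic term | 8.2–9.5% | 14.1–16.7% |
| 6-month contrast | 14.2–16.1% | 12.4–15.3% |
| 12-month contrast | 10.2–10.8% | 3.7–4.6% |

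Under a random intercept with complete data, the mean model SE for weight at 6 months is 0.46 lb against a true 0.64 lb. With the own-baseline covariate deleted, the random-intercept model gives 4.6–5.7% (joint) and 5.0–5.2% (6 months), with SE ratios of 0.99–1.01.

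**Simulation, all arms sharing a step at 3 months that is then held.** This is the trajectory the sample size section assumes (random intercept, complete data).

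| Common step | 4-df test | 6-month contrast |
|---|---|---|
| Weight, 11 lb (control-sized) | about 5–8% | about 9% |
| Pain, 2 units (control-sized) | about 9–10% | about 10–11% |
| STOP-sized (17 lb; 4 units) | about 3–4% | no material inflation |

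A quadratic cannot follow a step, and the misfit enlarges the residual variance, which offsets the shrinkage. Without the covariate, the same model is conservative here (about 0–2% on the joint tests).

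**Unstructured covariance.** The profile log-likelihood for the baseline coefficient is 365.9 at 0.89, 653.7 at 0.99, 930.0 at 0.999 and 1206.3 at 0.9999. Each tenfold step of the coefficient towards 1 from 0.99 adds 276.3 = 120 × ln 10, so there is no maximum.

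**The case against.** **The size depends on a flat mean.** A reader might infer that the plan as written simply triples the type I error. The documents do not support that as an unconditional statement: the power section assumes a step at 3 months that is maintained, and under that shape the error is roughly nominal to twice nominal on the 4-df test. This stands, and it limits the claim. It does not clear the model, because one misfit is then offsetting another. The actual trajectory is unknown in advance, and the covariate still shrinks the standard errors relative to the same model without it.

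**The covariance structure is not given.** Also true, and an analysis plan that is not shown may name it. The section describes individual change over continuous time, which points to random effects. With a random slope the 12-month contrast is not inflated, though the interaction terms are. An unstructured matrix shows no inflation but has no proper maximum, so it does not rescue the specification.

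**A harmless reading exists.** Controlling for the two baselines could mean the other outcome's baseline, or adjustment through the equal-means constraint. The text does not say so. It names both baselines for both outcomes alongside the constraint, and a programmer following it would enter both. If the harmless meaning was intended, the sentence still needs rewording.

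**The 6-month contrast is not the stated primary test.** Correct. The group-by-time terms are, and their error rates appear above in their own rows.

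**Conclusion.** The double use of baseline is in the text, and it biases the group-by-time standard errors downward. Under random-effects covariance, the plan's variance inputs and no mean change, type I error is about 13–19% for the 4-df group-by-time test and about 12–16% for the 6-month contrast. It is smaller or absent in two settings: where all arms share the assumed step (random intercept: about 5–10% on the 4-df test for the control-sized step, 3–4% for the STOP-sized one), and for the 12-month contrast with a random slope. With an unstructured covariance the problem is a degenerate likelihood, not inflation.

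These figures assume 1:1:1 allocation, two-sided tests and compound-symmetric data. The step-change results were obtained for a random intercept only. That the specification should change is firm; how large the inflation would be in this trial is not.

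**What to change.** Use the outcome's own baseline once. Keep baseline in the outcome vector with equal arm means, and delete that outcome's own baseline from the covariates. Baseline pain may stay as a covariate in the weight model, and baseline weight in the pain model. Name the covariance structure in the same place. This costs a sentence or two in the analysis section, with no participants and no new data.

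Modelling only 3, 6 and 12 months with own baseline as covariate is not a drop-in replacement. Under the plan's assumption the STOP–SCW difference is 6 lb at every follow-up visit, so its change over follow-up is 6 − 6 = 0. The whole effect sits in the arm main effect, and a group-by-time test alone would miss it. If that form is chosen, the primary test must be redefined to include the arm main effect, for example as arm differences at 6 and 12 months. That form also leaves out anyone with no follow-up visit, which has to be squared with the stated intent to include every randomised participant.

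Deleting the covariate does not settle whether a quadratic suits a step-shaped response; that is a separate matter.
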